# A single-center, open-label, randomized, parallel-group trial to pilot the effectiveness of a peer coach behavioral intervention versus an active control in reducing anxiety and depression in patients scheduled for total knee replacement

**DOI:** 10.1186/s12891-023-06460-4

**Published:** 2023-05-05

**Keywords:** Knee osteoarthritis, Knee replacement, Peer coach, Home physical therapy, Cognitive behavioral therapy

## Abstract

**Background:**

*Moving Well* is a behavioral intervention for patients with knee osteoarthritis (KOA) scheduled for a total knee replacement (TKR). The objective of this intervention is to help patients with KOA mentally and physically prepare for and recover from TKR.

**Methods:**

This is an open-label pilot randomized clinical trial that will test the feasibility and effectiveness of the *Moving Well* intervention compared to an attention control group, *Staying Well*, to reduce symptoms of anxiety and depression in patients with KOA undergoing TKR. The *Moving Well* intervention is guided by Social Cognitive Theory. During this 12-week intervention, participants will receive 7 weekly calls before surgery and 5 weekly calls after surgery from a peer coach. During these calls, participants will be coached to use principles of cognitive behavioral therapy (CBT), stress reduction techniques, and will be assigned an online exercise program, and self-monitoring activities to complete on their own time throughout the program. *Staying Well* participants will receive weekly calls of similar duration from research staff to discuss a variety of health topics unrelated to TKR, CBT, or exercise. The primary outcome is the difference in levels of anxiety and/or depression between participants in the *Moving Well* and *Staying Well* groups 6 months after TKR.

**Discussion:**

This study will pilot test the feasibility and effectiveness of *Moving Well*, a peer coach intervention, alongside principles of CBT and home exercise, to help patients with KOA mentally and physically prepare for and recover from TKR.

**Trial registration:**

Clinicaltrials.gov. NCT05217420; Registered: January 31, 2022.

**Supplementary Information:**

The online version contains supplementary material available at 10.1186/s12891-023-06460-4.

## Contributions to the literature

This clinical trial will pioneer the use of peer coaches for TKR. Peer coaches will have a similar medical profile (age group, history of KOA and TKR) to patientsThis clinical trial will be the first home-based, telephone delivered pre- and post-operative program. The use of the internet and telephone simplifies the logistics of intervention delivery, facilitating wide scalability of the program.This clinical trial addresses patient pain catastrophizing, depression, and anxiety through CBT for the first time in a pre- and post-operative program for patients with knee OA undergoing TKR.

## Background

Osteoarthritis (OA) is a common condition affecting an estimated 31 million mostly older US adults between 2008 and 2011 [1]. Knee OA (KOA) can be profoundly debilitating, negatively impacting mobility. Total knee replacement (TKR) is an effective strategy to improve knee function and quality of life, however, up to 30% of patients with TKR continue to experience knee pain after surgery [2–4]. Poor prognostic indicators include obesity, pre-operative deconditioning, high levels of anxiety and/or depression, and pain “catastrophizing” (overemphasis on negative aspects or consequences of an experience) before TKR [5–21]. Yet few interventions have focused on optimizing both mental and physical health in patients with KOA before and after TKR, especially in patients with these risk factors

One approach is to add pre-habilitation (pre-hab) to post-TKR rehabilitation. A meta-analysis of post-TKR interventions did not show differences in self-reported pain > 12 months after TKR, except for one telephone-delivered, home-based intervention of functional exercises delivered by physical therapists, aimed at managing anxiety related to knee pain [22, 23]. This suggests that post-operative interventions alone may be insufficient. However, studies with pre-hab interventions for joint replacement surgery suffer from methodological shortcomings [24, 25]. In a study by Wang et al. on total hip arthroplasty patients [26], the pre-hab intervention group also received an intensive post-operative exercise program, making it difficult to attribute benefits to the pre-hab intervention alone. A consistent challenge in pre-hab programs was low adherence, potentially because they required in-person interaction with the physical therapist [24, 25]. Hence, having a well-designed, feasible intervention, with pre-hab and rehabilitation components that addresses mental and physical health, can serve as a viable alternative to improve post-TKR pain among patients with KOA.

Several studies have shown strong associations between high levels of anxiety, depression, and negative surgery expectations with worse TKR outcomes [5, 16, 20, 21]. These associations were independent of other factors related to persistent pain and low physical function after TKR. Patients with high pain catastrophizing pre-operatively had 2.67 (95% CI, 1.2–6.1) higher odds of < 50% post-operative improvement in pain after adjustment for potential confounders [16]. This evidence emphasizes that in addition to physical health, mental health has a strong influence on TKR outcomes, yet few interventions have targeted these factors.

Cognitive behavioral therapy (CBT) is a type of psychotherapy that teaches patients how to modify dysfunctional thinking and behavior to solve active problems [27, 28]. CBT has been shown to significantly reduce pain, anxiety, depression, and insomnia among patients suffering from headaches, osteoarthritis pain, depression, and insomnia [29–31]. CBT has so far been mainly studied as a way to treat symptoms of OA, and not as a strategy to help patients prepare and recover from TKR [32, 33]. One study that examined pre-TKR CBT for reducing pain catastrophizing and improving pain outcomes after total knee replacement, found no improvement in 3-month pain outcomes after surgery in the intervention group when compared to a non-CBT control [34], indicating that CBT interventions alone may not be sufficient in improving outcomes after TKR.

Peer coaches, also called community health workers, are lay individuals with a specific diagnosis that work with a patient population with the same condition to improve disease management. Peer coaching interventions leverage the interpersonal connection and support between peer and patient to increase patient confidence in achieving favorable outcomes [35]. Studies utilizing peer coaches have demonstrated increased medication adherence among patients with human immunodeficiency virus, asthma, diabetes, and increased cancer screening [36–45]. The social and emotional support peer coaches provide to patients living with the same condition can lead to positive behavior change and engagement and participation in medical decisions related to their condition.

*Moving Well* is a peer-coach delivered intervention that will incorporate pre-habilitation and principles of CBT, with the standard of care for patients undergoing TKR, in order to pilot test the hypothesis that levels of anxiety and depression will be lower in participants in the intervention group, compared to baseline and the attention control group, *Staying Well,* at 6, 12, and 24 months post-TKR. A secondary hypothesis is that participants in the *Moving Well* intervention group will have less knee pain at 6, 12, and 24 months post-TKR compared to the *Staying Well* attention control group.

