### Primary and secondary outcomes

The primary outcome will be the difference in levels of anxiety and depression 6-, 12-, and 24-months post-surgery between *Moving Well* and *Staying Well*. The GAD-7 [54] and PHQ-8 [55] will be used to assess the participants’ level of anxiety and depression respectively. Participants will complete the data collection survey at baseline, 6-, 12-, and 24-months post-surgery. If participants have not completed the data collection surveys, a blinded member of the research team will follow up with a phone call to complete the forms over the phone and minimize missing data.

Secondary outcomes will include change from baseline to 6-, 12-, and 24-months post-surgery in the level of social support, general health status, level of pain catastrophizing, knee pain and function, level of self-efficacy, level of sleep disturbance, and opioid use for knee pain. Table 4 has details of the instruments that we will be using to measure primary and secondary outcomes and the time points that data collection will occur. These secondary outcomes will be measured respectively using the following: Lubben Social Network Scale-18 (LSNS-18) [56], 12-Item Short Form Survey (SF-12) [57], Pain Catastrophizing Scale (PCS) [58], Knee Injury and Osteoarthritis Outcome Score (KOOS) Pain and Activities of Daily Living (ADL) sub-scales [59], General Self-Efficacy Scale (GSF) [60], Patient-Reported Outcomes Information System (PROMIS) Sleep Disturbance Scale [61], and participant self-report use of opioids for knee pain.

**Table 4 Tab4:** Data collection timepoints and respective outcomes

	**Baseline**	**1-week pre- surgery**	**6-weeks post- surgery**	**6-months post-surgery**	**1-year post- surgery**	**2-years post-surgery**
Sociodemographic information (collected via EHR and patient survey)	x					
Medical history (collected via EHR and patient survey)	x					
Surgical history (collected via EHR and patient survey)	x					

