### Data analysis

We will use descriptive statistics, t-tests, and Chi-square tests as appropriate to compare patients in each study arm. We will assess group differences between baseline and the week before TKR, 6 weeks after TKR, and 6-, 12-, and 24-months after TKR with parametric and nonparametric analyses including one-sample t-tests, Wilcoxon rank sum, and Chi-square tests or Fisher’s exact test of proportions, as appropriate. All tests will be two-sided (unless otherwise stated) and the overall type I error will be maintained at 5%.

We will use linear and generalized linear mixed effects regression models to analyze the repeated measures of all outcomes. Although a significant treatment*time interaction will conclude rejection of the hypothesis, in this pilot study we will focus on obtaining estimates of baseline adjusted treatment effects at the end of treatment as preliminary evidence of effectiveness to power a future trial. We will correct the inflation of the type I error due to multiple primary outcomes using Holm’s stepdown procedure. Due to the exploratory nature of the secondary outcomes, we will not adjust the type I error. Our mixed models provide valid inferences when data are missing at random. However, we will also test the plausibility of this assumption and repeat our analysis using pattern-mixture models [65].

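### The main hypothesis and one listed test compare the intervention arm with its own pre-surgery baseline, which does not test the intervention and does not match the between-arm primary outcome

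*Protocol article*

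**What the plan says.** The last paragraph of Background gives the main hypothesis: anxiety and depression will be lower in the Moving Well arm at 6, 12 and 24 months after surgery, "compared to baseline and the attention control group". The next sentence gives the secondary hypothesis, on knee pain, against Staying Well only.

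The first paragraph of Data analysis says "We will assess group differences between baseline and the week before TKR" and each later visit, using "parametric and nonparametric analyses including one-sample t-tests, Wilcoxon rank sum, and Chi-square tests" or Fisher's exact test. It does not say which test serves which purpose, and it does not label change within an arm as descriptive.

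The rest of the article is built on a between-arm comparison:

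- Abstract, Methods: "The primary outcome is the difference in levels of anxiety and/or depression between participants in the" two groups, at 6 months.
- Primary and secondary outcomes: "The primary outcome will be the difference in levels of anxiety and depression 6-, 12-, and 24-months post-surgery between" the two arms.
- Study population and sample size: the power statement is for a 0.5 SD difference between the intervention and attention control arms.
- Data analysis, second paragraph: "We will use linear and generalized linear mixed effects regression models to analyze the repeated measures of all outcomes", and "a significant treatment*time interaction will conclude rejection of the hypothesis", with the emphasis on baseline-adjusted treatment effects and Holm's procedure for the two primary outcomes.

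**The concern.** Baseline is taken before surgery and the 6-, 12- and 24-month visits come after it. Under the guidelines for cancellation and postponement, a participant whose surgery is cancelled or delayed by more than two weeks leaves the study schedule and no further data are collected. Those with post-surgery scores have therefore had the operation, which Background itself describes as effective for function and quality of life. A fall in PHQ-8 or GAD-7 within one arm could come from the intervention, the operation, the passing of the anticipation of surgery, time or regression to the mean. A one-arm comparison cannot tell these apart.

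A one-sample t-test uses one sample. Applied to change scores, it tests whether one arm changed, not whether the arms differ. With the baseline comparator written into the main hypothesis, the plan gives an uncontrolled pre-post comparison a place in the hypothesis and a route to a p-value. The pilot is meant to supply preliminary evidence of effectiveness for a larger trial, so a significant within-arm change could be put forward as part of that evidence when the between-arm effect is nil.

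**Working it through.** **1. Does any stated figure depend on the comparison with baseline?**

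Inputs from Study population and sample size: d = 0.5 between arms, at least 80% power, four repeated measures, ICC 0.05 to 0.20, overall 5% split by Bonferroni over two outcomes (0.025 each), 20% attrition, 37 per arm, 93 recruited.

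SD of the mean of m measures = sqrt((1 + (m − 1) × ICC) / m), and n per arm = 2 × (z for 1 − 0.025/2 + z for 0.80)² × SD² / 0.5².

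| Measures averaged | ICC | n per arm needed | Power at 37 per arm |
|---|---|---|---|
| 3 (post-baseline) | 0.20 | 36 | 81.8% |
| 4 | 0.20 | 31 | 87.7% |
| 4 | 0.05 | 22 | 96.2% |

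Recruitment: 74 / (1 − 0.20) = 92.5, rounded up to 93, as stated.

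The planned 37 per arm is reproduced closely with three post-baseline measures and exceeded in the other two rows. All of it concerns the between-arm contrast. Nothing in the sample size rests on a comparison with baseline.

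**2. How often would a within-arm test be significant if the intervention did nothing?**

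Taken from the article: n = 37 in the arm and two-sided 5%. Its ICC range of 0.05 to 0.20 is used as the pre-post correlation ρ. Assumed, because the article gives neither: a fall shared by both arms of 0.3 or 0.5 SD, and ρ = 0.6 as a higher case.

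SD of change = sqrt(2(1 − ρ)). Noncentrality = fall / SD of change × sqrt(37). The critical value is t(36) = 2.028.

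| Shared fall (SD) | ρ | SD of change | Noncentrality | P(significant) |
|---|---|---|---|---|
| 0.5 | 0.05 | 1.378 | 2.206 | 57% |
| 0.5 | 0.20 | 1.265 | 2.404 | 65% |
| 0.5 | 0.60 | 0.894 | 3.400 | 91% |
| 0.3 | 0.05 | 1.378 | 1.324 | 25% |
| 0.3 | 0.20 | 1.265 | 1.443 | 29% |
| 0.3 | 0.60 | 0.894 | 2.040 | 51% |

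At two-sided 2.5% and ρ of 0.05 to 0.20, the figures are 46-53% for 0.5 SD and 17-20% for 0.3 SD.

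These are probabilities of detecting a real fall that both arms share. They are not error rates of the primary analysis. A between-arm test in the same situation stays at its nominal level whatever improvement the arms share.

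**The case against.** The strongest reply is that the inference is already between arms. The primary outcome, power, treatment-by-time criterion and baseline-adjusted estimate all compare two randomized arms that both undergo surgery, so shared recovery cancels. The hypothesis also joins its two comparators with 'and': read literally, a fall from baseline without a difference from Staying Well does not satisfy it. Nothing in the article says that a within-arm change alone would count as effectiveness. All of this stands, and it limits the point to a supplementary comparison.

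A reader might infer more in four places, and the article does not support it:

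- *That surgical recovery is credited to the intervention in the primary analysis, or that the attention control is wasted.* The formal analysis uses that control.
- *That the rank-sum test is wrong.* It compares two independent samples and is valid for change scores between arms. No text applies it to one person's baseline and follow-up scores, so an argument about unpaired standard errors has no basis either.
- *That the simple tests escape the multiplicity correction.* The paragraph listing them says overall type I error is held at 5%, and Holm's procedure follows for the primary outcomes. The text does not settle where the simple tests fall.
- *That the rejection rates forecast this trial.* They depend on assumed falls.

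It can also be said that matching tests to variables is detail a condensed article leaves to the full plan. That does not cover this point: the baseline comparator and the one-sample t-test are stated text.

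**Conclusion.** The point holds in a limited form. The main hypothesis contains an uncontrolled comparison with a pre-surgery baseline, and Data analysis names a test that cannot compare arms. Both disagree with the between-arm outcome, power statement and decision criterion elsewhere in the article, which remain sound. What is at stake is a misleading supplementary claim. With no intervention effect, a within-arm test in 37 people would be significant 57-65% of the time for a shared 0.5 SD fall and 25-29% for 0.3 SD at correlations of 0.05 to 0.20, rising to 91% and 51% at 0.6. The falls and the 0.6 correlation are assumptions, as is reading the article's ICC as the pre-post correlation. That the comparison is uncontrolled does not depend on them. It should be corrected because the correction costs almost nothing.

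**What to change.** - **Background, main hypothesis:** delete the reference to baseline as a comparator, so that the sentence contrasts Moving Well with Staying Well, as the secondary hypothesis already does.
- **Data analysis, first paragraph:** for PHQ-8 and GAD-7, replace the one-sample t-test with the baseline-adjusted between-arm contrast from the mixed model. If a simple check is wanted, use a two-sample t-test or rank-sum test on change scores between arms.
- **Same paragraph:** state that change within an arm is descriptive, shown as means with confidence intervals, and is not evidence of effectiveness.

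The cost is wording in two sections. The sample size stays at 37 per arm, 74 completers and 93 recruited, and the primary outcome, the mixed models and Holm's procedure are unchanged.

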## Methods

### Theoretical framework and implementation framework

The *Moving Well* peer coach intervention is guided by Social Cognitive Theory (SCT) [35]. This theory posits three mechanisms of human agency: direct personal agency (self-efficacy), proxy agency (reliance on others, such as parents or partners, acting at one’s behest to secure desired outcomes), and collective agency (coordinated interdependent efforts). Table 1 shows how the intervention maps to SCT by listing barriers people with KOA face in the effective participation of their own care and matches these barriers to their related theoretical constructs of SCT. It also maps each *Moving Well* session activity to each construct of the theory. We will use the Reach, Effectiveness, Adoption, Implementation, Maintenance (RE-AIM) framework for the implementation and evaluation of the *Moving Well* intervention [46].

**Table 1 Tab1:** Moving Well peer coach intervention mapping to social cognitive theory

Theoretical Construct	Targeted Barrier	Intervention Activity	Corresponding Session
**Self-Efficacy**	Anxiety Fear of pain Depressive symptoms Feeling isolated	Positive Thinking Coaching Motivational Interviewing Empowerment	Sessions 1 -7
**Outcome Expectation**	Catastrophizing Unrealistic expectations from total knee replacement	Action planning Motivational Interviewing	Sessions 1—7
**Socio-Cultural Factors**	No place to exercise No partner Lack of understanding of the value of exercise	Supportive coaching Action planning Education (PALS) Exercise program	Sessions 1–12

*PALS* Patient Activated Learning System

### Study population and sample size

The participants of the study will be people with KOA who are 50 years of age or older, have a TKR scheduled in 8 weeks or more, speak English, have access to a computer, the internet, and a working phone. We will exclude people who are unable to exercise (wheelchair-bound or bedbound), have a history of any joint replacement surgery, or have any rheumatic disease other than KOA.

The peer coaches of *Moving Well* will be people with KOA who had a TKR at least 12 months before they initiate their training as peer coaches of the intervention. This study will have 5 peer coaches.

The sample size estimation assumed four repeated measures, a range of intra-class correlations (0.05 to 0.20) for the repeated measures, and a Bonferroni-adjusted overall type I error of 5% (after controlling for two primary outcomes). We estimate a 20% attrition rate and will recruit 93 subjects, resulting in 37 participants in each arm of the study (total of *N* = 74 completers). The trial is designed to have at least 80% power to detect a standardized effect size of d = 0.5 or 0.5 standard deviations between the intervention and attention control arms. The standardized effect size is equivalent to a 2.7-point change in the PHQ-8 score, and a 1.6-point change in the GAD-7 score.

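### The 80% power at d = 0.5 fits an effect averaged over visits, but no section names such an average as the primary contrast; for a single visit, power is about 45–47% under the stated correlations

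*Protocol article*

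**What the plan says.** All references are to the protocol article.

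- **Study population and sample size.** The calculation "assumed four repeated measures, a range of intra-class correlations (0.05 to 0.20) for the repeated measures", with the overall 5% error Bonferroni-adjusted for two primary outcomes. On numbers: "We estimate a 20% attrition rate and will recruit 93 subjects, resulting in 37 participants in each arm of the study". On power: "The trial is designed to have at least 80% power to detect a standardized effect size of d = 0.5". The effect is equated to 2.7 PHQ-8 points and 1.6 GAD-7 points. The section does not say whether d refers to one visit or to an average, nor which four measures are meant.
- **Abstract, Methods.** "The primary outcome is the difference in levels of anxiety and/or depression between participants in the" two groups, at 6 months after TKR.
- **Table 5.** PHQ-8 and GAD-7 are primary, with the time frame given as baseline and 6-month follow-up.
- **Background (hypothesis) and Primary and secondary outcomes.** Both list 6, 12 and 24 months. Neither says that the visits are averaged.
- **Data analysis.** Mixed models are fitted to the repeated measures, a treatment-by-time interaction is mentioned, Holm's procedure covers the primary outcomes and tests are two-sided. The stated emphasis is that "we will focus on obtaining estimates of baseline adjusted treatment effects at the end of treatment".

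**The concern.** A power statement has to refer to the contrast that will be tested. Repeated measures with low within-person correlation sharply reduce the variance of an average over visits. They do little for a comparison at one visit. Here the power rests on four measures with correlations of at most 0.20, while the Abstract and Table 5 place the primary outcome at one visit and the analysis section focuses on one time point.

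If 6 months is the primary contrast, the stated 80% does not describe it. Readers who size the planned larger trial from this pilot, or who interpret its 6-month result, would then rely on a power figure that belongs to a different quantity.

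**Working it through.** **Inputs from the protocol article**
- 37 completers per arm; d = 0.5; ICC 0.05 to 0.20 (sample size section).
- Two primary outcomes under Bonferroni: 0.05/2 = 0.025 per outcome. Tests are two-sided (Data analysis).
- Implied SDs: 2.7/0.5 = 5.4 for PHQ-8 and 1.6/0.5 = 3.2 for GAD-7.
- Recruitment: 74/(1 − 0.20) = 92.5, rounded up to 93. This agrees with the plan.

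**Method.** Noncentral t with 72 degrees of freedom and noncentrality (0.5/s)·√(37/2), where s is the SD of the contrast in units of the single-visit SD. Equal correlation r between visits is assumed.

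**Step 1. Reproducing the stated figure.** For an average of m visits with a constant effect, s² = (1 + (m − 1)r)/m.

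| Contrast | r = 0.05 | r = 0.20 |
|---|---|---|
| Mean of 4 measures | s² = 0.2875, power 95.5% | s² = 0.400, power 86.4% |
| Mean of 3 follow-ups | s² = 0.367, power 89.4% | s² = 0.467, power 80.3% |

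So at least 80% is correct for a visit average across the whole stated range. The three-visit average at r = 0.20 needs 36 per arm by the normal approximation, against 37 planned.

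**Step 2. Single visit, unadjusted.** s² = 1, so the noncentrality is 0.5·√18.5 = 2.15 against a critical value of 2.29. Power is 44.9%. At 0.05 (second Holm step, once the other outcome is rejected) it is 56.4%. Reaching 80% at 0.025 would need 78 per arm.

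**Step 3. Single visit, baseline-adjusted**, which is closer to the planned analysis. s² = 1 − r², with r the baseline-to-follow-up correlation.

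| r | s² | Power at 0.025 | Detectable d at 80% |
|---|---|---|---|
| 0.05 | 0.9975 | 45.0% | 0.73 |
| 0.20 | 0.96 | 46.6% | 0.71 |
| 0.5 (assumed) | 0.75 | 57.9% | 0.63 |
| 0.6 (assumed) | 0.64 | 65.5% | 0.58 |
| 0.7 (assumed) | 0.51 | 76.3% | 0.52 |

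In scale points, d = 0.71 is 0.71 × 5.4 = 3.8 on PHQ-8 and 0.71 × 3.2 = 2.3 on GAD-7. At d = 0.52 the figures are 2.8 and 1.7.

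**Step 4. Other candidates within r = 0.05 to 0.20** (normal approximation, 0.025). A 6-month change score has s² = 2(1 − r) and power of 25–29%. A linear treatment-by-time slope over four equally spaced visits, ending in a difference of 0.5, has 28–33%. Neither reproduces 80%.

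**Step 5. Baseline-adjusted mean of 6, 12 and 24 months.** s² = (1 + 2r)/3 − r².

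| r | 0.05 | 0.2 | 0.3 | 0.5 | 0.7 |
|---|---|---|---|---|---|
| s² | 0.364 | 0.427 | 0.443 | 0.417 | 0.310 |
| Power | 89.6% | 84.0% | 82.4% | 84.9% | 94.0% |

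This contrast stays above 80% throughout.

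**The case against.** The strongest reply is that nothing has been miscalculated: the stated power follows from the stated inputs if d is a visit-averaged effect. The hypothesis and the outcomes section list three follow-ups, and the analysis fits mixed models to repeated measures. This stands. A reader might infer that the sample size contains an arithmetic error, or that the trial simply has 45% power for its primary endpoint. The documents support neither. Averaging is an inference from the figures, and 6 months is only one of the time points given for the primary outcome.

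It is also fair that the end of treatment is not clearly 6 months. The calls stop five weeks after surgery, so the nearest scheduled assessment in Table 4 is at 6 weeks. Data analysis therefore supports a single-time-point reading, but not specifically the 6-month one.

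Baseline adjustment could help more than the stated correlations suggest. At r = 0.75 single-visit power would be 83%. That lies outside the range used for the sample size, and an unadjusted four-visit average already falls to 67% at r = 0.5, so a high correlation would not rescue both readings. A reader might go further and call the stated ICC range optimistic. The documents give no observed within-person correlation, so that cannot be concluded; the higher values here are sensitivity assumptions only.

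Finally, this is a pilot that emphasises estimation, lists its small sample as a limitation and leaves a fully powered test to a later trial. That lowers the consequence. It does not make an explicit power statement apply to a contrast that it does not describe.

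**Conclusion.** The concern holds as a mismatch between the basis of the power statement and an inconsistently defined primary contrast. At least 80% is right for an effect averaged over visits, which no section names as primary. For any single visit, including 6 months, baseline-adjusted power at d = 0.5 is 45–47% within the stated correlations and reaches 76% at an assumed correlation of 0.7. The detectable d at 80% power runs from about 0.71 (r = 0.2) to 0.52 (r = 0.7), and is 0.73 unadjusted.

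These figures assume 37 completers per arm, two-sided 0.025 (the first Holm step), d in single-visit SD units and, for the averages, equal correlations and a constant effect. How large the shortfall is, and whether there is one, depends on how the primary time point is settled. It should be fixed; the pilot's focus on estimation keeps it from being critical.

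**What to change.** First, state one primary time point or contrast, and make the Abstract, the hypothesis in Background, Primary and secondary outcomes, Table 5 and Data analysis agree on it. This includes saying which visit the end of treatment refers to. Then do one of the following.

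- **(a) Keep 6 months.** Restate the power at d = 0.5 as about 45–47% under the stated correlations, up to 76% at an assumed correlation of 0.7, with the matching detectable d of about 0.71 to 0.52. The cost is a less favourable stated power.
- **(b) Name the baseline-adjusted mean over 6, 12 and 24 months as primary.** With 37 per arm this has 82–94% power for correlations of 0.05 to 0.7, given equal correlations and a constant effect. The cost is that the primary result becomes an average over two years rather than a 6-month effect.

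In either case, say in the sample size section which measures enter the calculation and whether d refers to one visit or to an average. Both options change wording only; neither adds participants or visits.
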